#### Statistical Plan

Mean, median, range and distribution of all baseline study variables will be determined (SPSS (13.0); site differences will be assessed using an Analysis of Variance (ANOVA). All primary and secondary outcome variables will be evaluated using an intention-to-treat analysis with a last observation carried forward (LOCF) for missing data, Paired t-tests will be used to calculate baseline changes in insulin parameters, body weight, BMI, cardiovascular risk factors, and related serum markers (adiponectin, leptin, ghrelin, resistin, C-reactive protein and other inflammatory markers, vitamin D and IGF-binding proteins at 6 and 12 months. Non-parametric measures will be used for comparison of group mean changes at 6 and 12 months. Statistical models will be used to calculate the primary (crude, non-adjusted) treatment effect of the respective study arms and for covariate adjustment by age, initial BMI category and menopausal status,

[figure not shown]

|  |                 |
|--|-----------------|
|  | and study site. |
|--|-----------------|

Publication / Presentation Plan:

Following the analysis of baseline data, abstracts will be submitted for presentation at annual meetings, including The Endocrine Society, The ADA, The American College of Cardiology, NAASO (The National Association for The Advancement of the Study of Obesity, NAMS, (The North American Society for Menopause). Publications will be prepared and submitted at regular intervals, following the collation of baseline data, and the completion of each study phase. A final summary manuscript will be submitted within 6 months of the study completion.

Estimated Study Budget/Requested Support (per patient cost, study medication, other supplies):

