|-------------------------------------------|---------------------------------------------------------------------------------------------------------------------------------------------------------------------------------------------------------------------------------------------------------------------------------------------------------------------------------------------------------------------------------------------------------------------------------------------------------------------------------------------------------------------------------------------------------------------------------------------------------------------------------------------------------------------------------------------------------------------------------------------------------------------------------------------------------------------------------------------------------------------------------------------------------------------------------------------------------------------------------------------------------------------------------------------------------------------------------------------------------------------------------------------------------------------|
|                                           | 
profiles at the 1, 2-, 3-, 6- and 12-month study visits (noted in Table 1).
 
GTT and insulin response curves will be obtained at baseline and at the end of 6 and 12 months in study completers.
 
Adverse events will be monitored and recorded by the study coordinators in accordance with IRB governance and guidelines at the three participating institutions. Serious adverse events (hospitalization, death or pregnancy) will be reported to GSK within 24 hours of obtaining SAE information.
                                                                                                                                                                                                                                                                                                                                                                                                                                                                                                                                                                                                                                           |

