| Outcome Parameters / Analytical Endpoints | 
The primary outcome variables are change from baseline in fasting and one-hour insulin at 1 year. Secondary outcome measures are 6 and 12 month change from baseline in body weight, CT scan-determined visceral adipose tissue other fat compartments, and relevant ratio's; total and multimeric adiponectin; and other cardiovascular risk and inflammatory markers, including lipids, c-reactive protein, TNF-<math>\alpha</math>, leptin, ghrelin, and resistin; and IGF-1 and IGF-binding proteins.
                                                                                                                                                                                                                                                                                                                                                                                                                                                                                                                                                                                                                        |
| Statistical Analysis Plan                 | 
Power Calculations and Assumptions
 
Three power calculations were performed incorporating the significance levels and sample size of TZD-based interventions in recently reported studies and comparator trials. A initial sample size of 25 per group is a realistic estimate and is based on the following assumptions:
 
 
1. Placebo treatment even with intensive dietary intervention (which will not be provided after the lead-in phase of EMPOWIR) has low rates of weight loss and high drop out rates at 6 and 12 months of study follow-up in the majority of published studies
 
2. data from observational and population based studies show annual weight gain in women in the study age range and BMI category
 
3. Metformin has a large treatment effect in hyperinsulinemic women and, in combination with hypocaloric carbohydrate modified diet, reduced fasting insulin by 25-40% and 1-hour (peak) insulin by 50% in our preliminary data. (with a mean body weight change 12.5% at 1-year).
 
4. Enrollment goals assume 10% drop out during Phase 2
 
 |

[figure not shown]

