#### Summary of sample size calculations:

The study design comprises 3 groups in one pre-treatment (Phase 1) and one post-treatment (Phase 3) measurement of outcome. Preliminary data from our open label use of metformin and other randomized clinical trials suggest that metformin affords large treatment effects. Nonetheless, as the large effect may be due in part to placebo, we will structure our sample size to detect more moderate treatment effects. Using an analysis of covariance, a sample size of 60 patients (20 per group) will provide at least 80% power to detect a moderate to large effect size ( $f=.38$ ) for a two-sided test of significance at a critical value of .05. While 20 patients per group are required to meet the anticipated effects, we will target 25 per group to allow for 20% attrition. The proposed attrition rate is less than rates reported in research studies of other medications evaluated for weight reduction, such as sibutramine (32%) and xenical (24%). However, the rate reflects attrition rates from our own preliminary data and from other published studies of patients treated with metformin analyzed using an intention-to-treat or comparable analysis such as studies of obesity in women, and children, PCOS, and HIV-related lipodystrophy.

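### Follow-up insulin is taken only in completers and gaps are filled by LOCF, so on the text shown a woman who leaves before month 6 is scored as no change

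*Protocol*

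**What the plan says.** - **Primary outcomes** (Outcome Parameters / Analytical Endpoints): these "are change from baseline in fasting and one-hour insulin at 1 year".
- **Insulin sampling** (Study Variables): "GTT and insulin response curves will be obtained at baseline and at the end of 6 and 12 months in study completers". The other bloods listed, at months 1, 2, 3, 6 and 12, are blood count, electrolytes and metabolic profiles. Insulin is not named among them. The row refers to a Table 1 that is not shown.
- **Missing data** (Statistical Plan): "All primary and secondary outcome variables will be evaluated using an intention-to-treat analysis with a last observation carried forward (LOCF) for missing data".
- **Drop-out**: the sample size summary says "we will target 25 per group to allow for 20% attrition". Item 4 of the power assumptions adds "Enrollment goals assume 10% drop out during Phase 2". Item 1 says that placebo treatment, in most published studies, "has low rates of weight loss and high drop out rates at 6 and 12 months of study follow-up".
- **Re-assignment** (Objective and Overview; Study Design): placebo women move to one of the two active arms after 6 months.

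The protocol describes no insulin test at withdrawal.

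**The concern.** Carrying a value forward needs a value to carry. With curves at baseline, month 6 and month 12 only, a woman who leaves in Phase 1 has nothing after baseline, and LOCF turns her missing result into a measured change of zero. One-hour insulin requires the glucose load, so an interim blood draw without a tolerance test could not supply it.

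Three consequences follow.

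- **Dilution.** If drop-outs would have changed like the women who stayed, each arm's mean change shrinks in proportion to its Phase 1 drop-out.
- **False differences.** All arms receive the diet, and the sample size summary concedes that part of the large metformin effect may be placebo. If insulin falls in every arm, unequal drop-out alone separates the arms. Month 6 is most exposed, because it is the only time at which the randomised placebo group can be compared with active treatment.
- **Mixed treatments at month 12.** A placebo-origin woman who leaves in Phase 2 contributes an on-placebo month-6 value to a 12-month result that is meant to reflect active treatment.

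The intention-to-treat label suggests protection against drop-out that this combination does not give.

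**Working it through.** **The plan's own figure.** 20 per group with 20% attrition: 20 / (1 − 0.20) = 25 per group, 75 in total. This reproduces.

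**How many women are scored as zero.** Inputs: 20% attrition in total (sample size summary) and 10% in Phase 2 (power assumptions, item 4). Taking the 10% as a share of those who enter Phase 2:

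- Phase 1 drop-out = 1 − 0.80/0.90 = 11.1%, and 75 × 0.111 = 8.3, so about 8 women carry baseline.
- Phase 2 drop-out: 75 × 0.889 × 0.10 = 6.7, so about 7 women carry month 6. If spread evenly, about 2 of these (6.7/3 = 2.2) are placebo-origin.
- Upper bound: if all drop-outs leave in Phase 1, 75 × 0.20 = 15 women carry baseline.

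**Dilution.** Observed mean change = true change × (1 − d), where d is Phase 1 drop-out. This assumes that drop-outs would have changed like completers and, at month 12, that month-6 values carried forward equal the 12-month change. The 25–40% and 50% rows are the falls reported for metformin plus diet in power assumptions item 3; 30% is an illustrative value inside the fasting range.

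| True fall | d = 11.1% | d = 20% |
|---|---|---|
| 25% (fasting, low) | 22.2% | 20% |
| 30% | 26.7% | 24% |
| 40% (fasting, high) | 35.6% | 32% |
| 50% (one-hour) | 44.4% | 40% |

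**False difference with no drug effect.** The protocol gives no drop-out rate by arm. Assume 30% on placebo and 10% on active treatment in Phase 1, and the same true fall c in all women. The spurious difference is c × (0.30 − 0.10) = 0.20c:

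- c = 5%: 1 point
- c = 10%: 2 points
- c = 30%: 6 points (−21% against −27%)

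**Effect on the test.** Simulation with 25 per arm, normally distributed changes with SD 1, random drop-outs set to zero, and the same true change in all arms (assumed):

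- Equal drop-out: type I error about 5%.
- 20/6.5/6.5% (mean 11%), change of −1 SD: about 8%.
- 32/10/10%, change of −1 SD: 12% with ANOVA, 15% with Kruskal-Wallis. With a change of −0.5 SD: 7% with ANOVA.

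With real effects at the protocol's f = 0.38, equally spaced means and equal drop-out, simulated ANOVA power is 83% with no drop-out, 77% with 11% set to zero and 70% with 20% set to zero. Twenty completers per arm alone give 73%. These runs ignore any gain from baseline adjustment, so only the comparisons between them matter. At 20% drop-out, the five imputed women per arm add no power.

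**The case against.** The strongest case on the other side has four parts.

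1. **Zero may be right.** If women who stop return to their baseline insulin, zero change is about correct for a question that counts what happens after stopping. This stands as a possibility, but the protocol does not claim it and plans no measurement that could show it.
2. **The numbers can be made too large.** A reader might take all 15 expected drop-outs as zero-scored, or apply the 30–50% falls to every arm and infer a false benefit of 6 to 10 points. The documents do not support either as the expected case. The 10% Phase 2 figure puts about half the drop-outs after month 6. The large falls were reported for metformin with diet, not placebo, and item 1 says that intensive dietary intervention will not continue after the lead-in. A common fall of 5–10%, also an assumption, gives 1 to 2 points.
3. **Unequal drop-out is not planned.** A reader might infer that drop-out will differ by arm. The remark on high placebo drop-out describes published studies, while the sample size applies one 20% rate to every group. Only that it may differ is supportable.
4. **This is a pilot with LOCF openly pre-specified, and sensitivity analyses may sit in an analysis plan not shown.** That lowers the severity. It does not remove the point, because both the sampling restriction and the LOCF rule are fixed in the protocol itself.

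A general claim that the standard errors are invalid would also go too far: with equal drop-out the simulated type I error stayed at about 5%.

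**Conclusion.** The concern holds and should be fixed, at moderate size. Completers-only sampling combined with LOCF scores Phase 1 drop-outs as no change: certainly for one-hour insulin, and for fasting insulin unless Table 1 lists earlier samples. On the protocol's own figures this affects about 8 of 75 women and turns a true 30% fall into about 26.7%; the bound, if all 15 leave in Phase 1, is 24%. A false difference between arms needs two things the protocol does not quantify: unequal drop-out and a fall shared by all arms. Under the assumed 30% and 10% drop-out it is 1 to 2 points for a 5–10% fall and 6 points for 30%.

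The direction is not fixed. Equal drop-out shrinks effects, while unequal drop-out can create or hide them. All these sizes assume that drop-outs would have changed like completers in their arm.

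**What to change.** 1. **Study Variables.** Replace the restriction to completers with: *in all randomised women, including those who stop study drug, unless consent is withdrawn*. This is the main fix, because no model can recover insulin values that were never measured.
2. **Statistical Plan.** Replace LOCF as the primary method with a likelihood-based repeated-measures model with terms for arm, visit, arm-by-visit, baseline and site. Keep women who have only a baseline value, either by treating baseline as an outcome in the model or by multiple imputation. A model that uses baseline only as a covariate would drop them.
3. **After month 6.** Use month 6 for the randomised comparison with placebo. From then on, model placebo-origin women by their re-assigned treatment.
4. **LOCF.** Retain it as a sensitivity analysis.

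The cost is mainly wording, plus effort and some expense to recall drop-outs for a tolerance test. The budget attachment is not shown, so it cannot be assumed that these tests are already paid for. For women who are not retrieved, the result rests on a missing-at-random assumption, which the report should state.

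### The trial is sized on ANCOVA, but the Statistical Plan makes a crude effect primary, compares changes non-parametrically and leaves baseline insulin out of the covariates

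*Protocol*

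**What the plan says.** Under Summary of sample size calculations, the design is set out as follows: "The study design comprises 3 groups in one pre-treatment (Phase 1) and one post-treatment (Phase 3) measurement of outcome". The power statement reads "Using an analysis of covariance, a sample size of 60 patients (20 per group) will provide at least 80% power" for an effect size of f = 0.38, "for a two-sided test of significance at a critical value of .05". Enrolment is then raised: "we will target 25 per group to allow for 20% attrition".

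The Statistical Plan section, a few lines later in the same table row, does not mention ANCOVA. It contains:

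- paired t-tests of change from baseline;
- for the comparison between arms: "Non-parametric measures will be used for comparison of group mean changes at 6 and 12 months", with no test named;
- in a separate sentence: "Statistical models will be used to calculate the primary (crude, non-adjusted) treatment effect of the respective study arms", with no model named;
- in that same sentence, covariate adjustment by age, initial BMI category, menopausal status and study site. Baseline insulin is not in the list.

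The Outcome Parameters / Analytical Endpoints row defines the primary outcomes as "change from baseline in fasting and one-hour insulin at 1 year". Glucose tolerance tests with insulin curves are scheduled at baseline, 6 months and 12 months, so the baseline values will be in hand.

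**The concern.** In a design with one pre- and one post-treatment measurement, the natural ANCOVA covariate is the baseline value of the outcome, and it is usually the covariate that removes most residual variance. The sizing invokes that method, but the analysis section uses it neither for the primary effect nor for the adjusted models. The sentence on group comparison also does not hang together: it applies non-parametric methods to differences in means, which rank tests do not compare.

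Two things are at stake. First, the stated power belongs to an analysis that is not planned. Second, with about 20 evaluable women per arm, an unadjusted change score carries all the noise of the baseline test, and that costs power the trial can ill spare. A smaller issue is that two candidate between-arm analyses are described and neither is designated as the primary test, so the choice could be made after the data are seen.

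**Working it through.** **Inputs from the protocol.** Three groups, N = 60 evaluable (20 per group), f = 0.38, alpha 0.05, stated power at least 80%, 25 per group randomised. **Assumed, because the protocol gives neither:** the baseline-to-follow-up correlation r (shown at 0.3, 0.5 and 0.7) and, for skewed data, a log-scale SD of 0.6.

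**1. The plan's own figures.** The attrition step reproduces: 60 / (1 − 0.20) = 75. For the three-group F test, the noncentrality is λ = f²N = 0.38² × 60 = 8.66, with 2 and 57 degrees of freedom (56 with one covariate). Power is 73%, and stays at 73% with 0 to 5 covariates. At N = 60, 80% power needs f = 0.41; at f = 0.38 it needs about 70 patients.

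**2. When 80% is reached.** If 0.38 is in unadjusted SD units, ANCOVA raises it to f / √(1 − r²). Reaching 0.4117 requires 1 − r² = (0.38 / 0.4117)² = 0.852, so r is about 0.39. At r = 0.4 power is 81%. The stated figure for the three-group test therefore needs baseline adjustment with r of about 0.39 or more. A one-degree-of-freedom test on all 60 would give 82%, but the sizing describes three groups.

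**3. Effect of dropping the baseline covariate, normal data.** For a change score the effect size is f / √(2(1 − r)). The variance ratio of ANCOVA to change score is (1 − r²) / (2(1 − r)) = (1 + r) / 2, that is 0.65, 0.75 and 0.85 at the three values of r. Kruskal-Wallis is given relative efficiency 0.955 against the F test.

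| r | f, ANCOVA | f, change | ANCOVA | ANOVA on change | Kruskal-Wallis on change |
|---|---|---|---|---|---|
| 0.3 | 0.398 | 0.321 | 77% | 57% | 55% |
| 0.5 | 0.439 | 0.380 | 85% | 73% | 71% |
| 0.7 | 0.532 | 0.491 | 96% | 92% | 91% |

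A crude comparison of final values, ignoring baseline, has 73% at every r.

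**4. If f = 0.38 is already covariate-adjusted.** ANCOVA has 73% throughout. Kruskal-Wallis on changes has 51%, 58% and 63%.

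**5. Skewed data, simulated.** 3000 trials per value of r, 20 per arm, log-normal insulin, both active arms 0.81 SD from placebo on the log scale. This matches the plan's effect size: 0.81 × √2 / 3 = 0.38. The Monte Carlo standard error is at most √(0.25 / 3000) = 0.9 points.

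| r | ANCOVA, log insulin | Kruskal-Wallis, log change | Kruskal-Wallis, raw change |
|---|---|---|---|
| 0.3 | 77% | 55% | 42% |
| 0.5 | 84% | 69% | 55% |
| 0.7 | 95% | 91% | 76% |

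The loss against log-scale ANCOVA is 22, 15 and 4 points on log change, and 35, 29 and 19 points on raw change.

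**6. Where these figures apply.** They describe a placebo-versus-active contrast. The overview and the study design row both move placebo patients to an active arm after 6 months, so that contrast exists at 6 months and not at 12. The primary outcome is set at 1 year, and the sizing ties the post-treatment measurement to a Phase 3, although the design numbers only Phases 1 and 2.

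**The case against.** Several objections have force.

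- **A reader might infer that the primary effect is tested by a rank method.** The protocol does not say so. The crude primary effect comes from unnamed statistical models, and the non-parametric comparison is a separate sentence. What stands is that neither is the ANCOVA of the sizing.
- **A reader might infer that adjustment is absent.** It is planned, with four covariates. It is not primary, and it omits baseline insulin.
- **A reader might infer that the power is given up for nothing.** Rank methods guard against skew, which is a fair worry for insulin. In a further simulation with log-normal data and equally spaced means at r = 0.5, Kruskal-Wallis on raw change beat ANOVA on raw change, 53% to 47%. That protection is available at lower cost: in the same simulation log-scale ANCOVA had 86% and rank ANCOVA 82%.
- **The loss depends on r, which is unknown.** At r = 0.7 without skew it is about 5 points. It is tempting to argue that selecting on AUC-insulin lowers r, but the protocol gives no figure for this and the simulation did not model the entry cut.
- **The sizing counts 60, while the plan is intention-to-treat with last observation carried forward.** With all 75 analysed at f = 0.38 the three-group test has 83%. That takes carried-forward values as full information, and the protocol's own statement rests on 60.
- **Details such as a log transform may sit in a separate SAP.** Agreed, and silence on the transform is not part of this point. The mismatch between sizing method, primary effect and covariate list is in the protocol's own text.

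**Conclusion.** The point holds as a mismatch and an avoidable loss of efficiency; it should be fixed. The analysis that justified 60 evaluable patients is not the analysis planned, and baseline-adjusted ANCOVA had more power at every r examined. On the unadjusted reading of f, the cost of rank tests on change is about 4 to 22 points on the log scale for r from 0.7 down to 0.3, and about 19 to 35 points on the raw scale with a log SD of 0.6. On the adjusted reading, ANCOVA itself reaches only 73%, so the stated 80% does not follow. These sizes rest on assumed values of r and of the log SD, and on a placebo contrast that is available only at 6 months.

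A reader might go further and conclude that the planned analyses are invalid. The documents do not support that: unadjusted comparisons of change in a randomised trial are unbiased and do not inflate type I error. In a self-described pilot, this is a matter of precision and consistency, not of validity.

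**What to change.** - Name one primary between-arm analysis that matches the sizing: ANCOVA of (log) insulin on arm, with the matching (log) baseline value and study site as covariates, fitted separately for fasting and 1-hour insulin. On the log scale, report between-arm ratios of geometric means with 95% confidence intervals.
- Keep the non-parametric comparison of changes as a sensitivity analysis, and name the test.
- State whether f = 0.38 is before or after covariate adjustment, give the assumed r, and restate the power for the three-group test.
- Reconcile the primary visit with the move of placebo patients to active treatment at 6 months, so that the ANCOVA refers to a stated contrast at a stated visit.

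The cost is wording. No new data are needed. The model spends about 3 degrees of freedom: 1 for baseline insulin and 2 for three sites. The Study Population section speaks of four centers; on that count it would be 4.

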| 
Study Design
          | 
Overview
<small>Please see attached Study Flow Chart</small>
 
Chart review of patients at the 3 study Centers and their affiliated General Medical and Gynecology practices and public announcements will be used to identify non-diabetic women who meet selection criteria who will be invited to participate in the study. After obtaining consent, and additional screening for suitability, 80 patients will undergo glucose tolerance testing and additional tests to determine if they meet study inclusion and exclusion criteria. Following a 1-month lead-in phase, an initial study population of 75 women from 3 clinical sites will be randomized to placebo (diet and lifestyle modification) or one of two active study treatment arms for a 6-month study (Phase 1); patients in the diet plus placebo group will then be crossed over to one of the two active study arms for a 2nd six months (Phase 2).
 |
| 
Inclusion / Exclusion
 | 
Inclusion Criteria
 
 
1. Healthy, non-diabetic women with "≥20 pound weight gain since their twenties"
 
2. Age: 35-55
 
3. Peri-menopausal ( FSH ≥25 on day 2-3 of cycle) or postmenopausal status
 
4. Body Mass Index (BMI) 25-35 kg/m^2
 
5. Either:             
 
(a). a single blood pressure recording ≥135/85 or the use of blood pressure medication
 
OR
 
(b) HDL≤50mg/dl or triglycerides ≥150 mg/dl or the use of lipid modifying medication
 
 
 
7. Area-under-the-curve (AUC-)insulin level ≥100μU/ml along with normal fasting (≤100 mg/dl) & postprandial (≤200 mg/dl) glucose determinations following a 75-gram standard oral glucose tolerance test.
 
 
Exclusion Criteria
                                                             |

[figure not shown]

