| Study Variables
(Clinical procedures, laboratory tests, safety assessments) | 
Weight, BMI, waist and hip circumference, blood pressure will be recorded and appetite ratings, exercise log and food dairies evaluated weekly for the first six weeks and monthly for Phase 1. During the study visits, a symptom check list will be used to inquire about new symptoms and any change in frequency or severity of preexisting (baseline) conditions. Bloods will be drawn for CBC, electrolytes, and comprehensive metabolic
 |
|--------------------------------------------------------------------------------|-------------------------------------------------------------------------------------------------------------------------------------------------------------------------------------------------------------------------------------------------------------------------------------------------------------------------------------------------------------------------------------------------------------------------------------------------------|

[figure not shown]

|                                           |                                                                                                                                                                                                                                                                                                                                                                                                                                                                                                                                                                                                                                                                                                                                                                                                                                                                                                                                                                                                                                                                                                                                                                     |

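### The covariate-adjusted model uses BMI as a category although it is measured as a number: a small loss of precision in the adjusted estimates only

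*Protocol*

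**What the plan says.** The Statistical Plan gives two roles to its statistical models in one sentence. They are to "calculate the primary (crude, non-adjusted) treatment effect of the respective study arms", and they are to provide "covariate adjustment by age, initial BMI category and menopausal status", with study site completing the list. The crude effect is therefore primary and the adjusted model is additional. The same section compares group changes at 6 and 12 months by non-parametric methods.

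BMI is available as a measurement. Under Study Variables, "Weight, BMI, waist and hip circumference, blood pressure will be recorded" at repeated visits, and Inclusion Criteria item 4 sets the entry range: "Body Mass Index (BMI) 25-35 kg/m" squared.

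The sample size summary starts from "Using an analysis of covariance" and states that "a sample size of 60 patients (20 per group) will provide at least 80% power" for an effect size of f = 0.38. It names no covariate and does not mention BMI.

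**The concern.** The protocol fixes the form of this covariate and picks the coarser one. This is therefore a stated choice, not a detail left for the statistical analysis plan. A category treats women at its two ends as alike, although entry spans only 10 kg/m². If BMI relates to the outcome roughly in a straight line, the grouped version explains less of the outcome's variance. The adjusted treatment effects then carry wider confidence intervals than the collected data allow.

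What is at stake is the precision of the adjusted estimates in a trial of 60 completers, or up to 75 women if everyone randomised is analysed with last observation carried forward. The adjusted model applies to secondary outcomes as well. These include body weight and visceral fat, for which a link with baseline BMI is plausible.

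**Working it through.** **The plan's own figure.** The protocol attaches no number to the BMI term. The nearest figure is the power statement. With three groups, N = 60, f = 0.38 and alpha 0.05, a noncentral F test with noncentrality f² × N = 0.1444 × 60 = 8.66 and 2 numerator degrees of freedom gives 73.0% power (72.9% with one covariate). The stated figure is at least 80%. An unnamed covariate explaining about 15% of outcome variance would close the gap. That is a separate matter, and nothing in the calculation relies on BMI category.

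**Inputs from the protocol.** BMI enters as a category; entry range 25 to 35 kg/m²; N = 60 (20 per group).

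**Assumed inputs, because the protocol gives neither.**
- r, the correlation of baseline BMI with the outcome. Strictly this is the partial correlation given the other covariates in the model.
- s, the share of BMI's variance that the categories keep.

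**Step 1: the share kept by a two-way split.**
- Normal BMI cut at the median: s = 2/π = 0.637.
- Uniform BMI on 25 to 35 cut at 30: total variance 10²/12 = 8.33; group means 27.5 and 32.5, so between-group variance is 2.5² = 6.25; s = 6.25/8.33 = 0.75.
- Truncated-normal shapes on 25 to 35 cut at 30 give about 0.65 to 0.69, inside this range.
- Three equal-width categories keep about 0.79 to 0.89.

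**Step 2: the loss.** With a linear relation, the residual variance under grouped BMI divided by that under continuous BMI is V = (1 − s r²)/(1 − r²). The standard error rises by √V − 1. The share of the sample effectively lost is 1 − 1/V.

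| r (assumed) | V, s = 0.75 to 0.637 | Increase in SE | Sample effectively lost |
|---|---|---|---|
| 0 | 1 | 0% | 0% |
| 0.1 | 1.003 to 1.004 | 0.13% to 0.18% | 0.3% to 0.4% |
| 0.2 | 1.010 to 1.015 | 0.52% to 0.75% | 1.0% to 1.5% |
| 0.3 | 1.025 to 1.036 | 1.23% to 1.78% | 2.4% to 3.5% |
| 0.4 | 1.048 to 1.069 | 2.35% to 3.40% | 4.5% to 6.5% |
| 0.5 | 1.083 to 1.121 | 4.08% to 5.88% | 7.7% to 10.8% |

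Worked line for r = 0.3 and s = 0.637: V = (1 − 0.637 × 0.09)/(1 − 0.09) = 0.9427/0.91 = 1.036, and √1.036 = 1.018. Of 60 women, 3.5% is about 2.

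**Step 3: three categories.** At r = 0.3, s = 0.79 gives V = 0.9289/0.91 = 1.021 and s = 0.89 gives V = 0.9199/0.91 = 1.011. The standard error rises by 0.5% to 1.0%, before the small cost of one more degree of freedom.

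**Step 4: power of the adjusted test.** With N = 60, f = 0.38 on the unadjusted standard deviation and r = 0.3, power is 75.6% to 76.1% with a two-way split and 77.2% with continuous BMI. The gain is at most 1.6 percentage points.

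**The case against.** Four objections deserve weight.

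- **The primary effect is crude.** This stands. A reader might infer that the precision of the main result, or the stated 80% power, is weakened by the BMI category. The protocol does not support that: the BMI term appears only in the additional model, and the sample size names no covariate.
- **The correlation is unknown and may be low.** This stands too. No figure in the protocol links baseline BMI to change in insulin, and a restricted entry range tends to lower a correlation. At r = 0.3 or below the cost is under 2% in standard error, and at r = 0 it is nil. A reader who takes the r = 0.5 row as the expected loss is relying on a favourable assumption. Even there, V = 1.121 means that 12% more women would be needed, which is the same as losing about 11% of the sample, not 12%.
- **A category is a legitimate covariate.** Correct. Grouping a baseline variable neither biases a randomised comparison nor inflates the type I error, so the choice is not an error in that sense. If the relation were markedly non-linear, a single straight-line term would not automatically do better. This limits the point to efficiency under a roughly linear relation.
- **Cut-points may be set elsewhere.** Their absence is no fault here. Any cut-points would still discard information under a linear relation; more categories would discard less.

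These objections shrink the point but do not remove it. The protocol gives no reason for grouping BMI, and the measured value is at hand.

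**Conclusion.** The point holds as a minor efficiency improvement to the covariate-adjusted model. For an assumed two-way split, the standard error of the adjusted estimates is larger by nothing at r = 0, by about 0.5% to 0.75% at r = 0.2, and by about 4% to 6% at r = 0.5. Three categories lose less. These figures rest on a roughly linear relation, on assumed values of r and on assumed cut-points. The crude primary effect and the planned sample size are unaffected, and no conclusion about the validity of the trial follows.

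**What to change.** In the covariate list of the Statistical Plan, replace the BMI category with baseline BMI as a continuous covariate, alongside age, menopausal status and study site. Age needs no change, because the protocol attaches the word category only to BMI. BMI categories can stay in descriptive tables. The change is a few words made before unblinding, uses data already collected, and has no cost in patients, visits or money.
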